**ACTRN12616001458426 linked to IBSM study NCT02867059**

## **PROTOCOL SYNOPSIS**

**Full Title:** Functional nuclear medicine imaging in subpatent malaria: a pilot study

**Short Title:** NA

**Project Number:** P2196

### **Objectives:**

Primary:

- To investigate the use of  $^{18}\text{F}$  FDG-PET/MRI to estimate the biodistribution of *P. falciparum* in human volunteer induced blood stage malaria studies.
- To investigate the use of  $^{18}\text{F}$  FDG-PET/MRI to estimate the biomass of *P. falciparum*.

Secondary:

- To describe the relative burden of organ-specific tissue sequestration in *P. falciparum*.
- To describe the impact of early malaria infection on glucose metabolism.
- To describe the MRI brain findings of early malaria infection in a prospective participant cohort.

**Population:** Two adult (male and female of non-childbearing potential) participants between 18 and 55 years of age, recruited from induced blood stage malaria (IBSM) model MAIN study populations (MAIN study refers to clinical trial QP15C20).

**Phase:** exploratory

### **Description of Investigation:**

Participants will receive a whole body PET/MRI scan and dedicated brain MRI one to three days prior to inoculation (within roughly one week prior) and on one to two days prior to confinement with peak parasitaemia post BSP inoculation (estimated InD 6 to 7). Preparation involves fasting for 6 hours prior, abstaining from excessive physical exertion and following a low carbohydrate diet 24 hours prior (recorded on a diet and activity sheet). Scans will be performed on the Biograph mMR PET/MRI system after the intravenous infusion of the standard radiotracer 2- $^{18}\text{F}$  fluor-deoxy-D-glucose(FDG) ( $^{18}\text{F}$  FDG) and MAGNETOM Prisma 3T MRI system. Collected images will be reviewed and reported by experienced radiologists specialising in MRI and nuclear medicine reporting. Quantification of  $^{18}\text{F}$  FDG uptake measurements will be established for intra-individual scans using Patlak model analysis and semi quantitative SUV measurement with reference to an  $^{18}\text{F}$  FDG external control.

**Study Duration:** October 2016 – June 2017

**Participant Participation Duration:** Estimated 8-14 days

**Estimated Time to Complete Enrollment:** August 2016 – March 2017

|                                                                             |           |
|-----------------------------------------------------------------------------|-----------|
| 1. KEY ROLES AND CONTACT INFORMATION .....                           | 9  |
| 1.1 Study Location(s) .....                                                 | 10        |
| 1.2 Study Management .....                                                  | 10        |
| 2. INTRODUCTION: BACKGROUND AND SCIENTIFIC RATIONALE .....           | 11 |
| 2.1 Background Information .....                                            | 11        |
| 2.2 Study Objectives .....                                                  | 12        |
| 3. STUDY DESIGN .....                                                | 14 |
| 3.1 Study Flow Chart .....                                                  | 15        |
| 4. PARTICIPANT ENROLLMENT AND WITHDRAWAL .....                       | 16 |
| 4.1 Recruitment .....                                                       | 16        |
| 4.2 Eligibility Criteria .....                                              | 16        |

## **2. INTRODUCTION: BACKGROUND AND SCIENTIFIC RATIONALE**

### **2.1 Background Information**

Morbidity and mortality from malaria infection remains significant despite anti-parasitic treatments. Understanding the pathophysiology of disease may aid in the development of adjunctive therapies to improve survival in severe cases. Parasite sequestration in tissue microvasculature permits evasion of the reticulo-endothelial system and increased biomass [1]. Organ specific sequestration contributes to end organ dysfunction in severe malaria syndromes. Owing to the inaccessibility of sequestered parasites, estimations of total biomass and sites of sequestration have historically relied on biochemical markers [2-5], animal models [1, 6, 7] and post mortem studies [8]. Determination of the biodistribution of malaria with functional nuclear medicine imaging may allow for more direct study of sequestration in human models. This may aid developing a better understanding of the organ dysfunction experienced in severe cases.

Nuclear medicine imaging techniques, particular hybrid PET/CT and PET/MRI have a central role primarily in oncology for assessing the biodistribution and activity of malignancy. The ability of these techniques to detect and locate biological and biochemical changes have more recently been applied to other medical fields including Infectious Diseases, though there are no studies in malaria.

This EXPLORATORY STUDY has been designed as a prospective pilot investigation to establish the role of  $^{18}\text{F}$  FDG-PET/MRI in studying the pathophysiology of subpatent malaria following low dose *Plasmodium falciparum* exposure in healthy adults. Collection of baseline and post inoculation imaging will provide information about changes in host/parasite glucose metabolism that may be used to estimate parasite biomass and biodistribution. Glucose uptake is increased up to 100-fold in parasitised erythrocytes [9], suggesting that  $^{18}\text{F}$  FDG may be a viable radiotracer to help evaluate the disease.

Whole body PET/MRI is a functional imaging modality that provides detailed soft tissue anatomical information with lower ionizing radiation exposure compared to equivalent PET/CT. The radiotracer  $^{18}\text{F}$  FDG is a safe and well-validated biomimetic for demonstrating glucose uptake. Imaging with  $^{18}\text{F}$  FDG-PET/MRI is an ideal model for exploring nuclear medicine functional imaging in a healthy human volunteer population.

Biochemical estimates of parasite biomass and parasitaemia will be compared to quantified radiotracer uptake measurements. Comparison of interval changes in host/parasite glucose metabolism will add to our understanding of the metabolic changes associated with disease [10]. Although there have been several trials using MRI imaging to study malaria, none to date have been prospective. Comparison of MRI brain data with existing literature in uncomplicated malaria may help further describe the changes seen in early disease [11]. The feasibility of  $^{18}\text{F}$  FDG-PET/MRI may contribute to developing a further role for nuclear medicine imaging in malaria.

Successful application of nuclear medicine imaging would provide a greater understanding of parasite sequestration dynamics, which may aid in disease modeling and development of treatments to prevent end organ damage in severe disease.

## 2.2 Study Objectives

Primary:

- To investigate the use of  $^{18}\text{F}$  FDG-PET/MRI to estimate the biodistribution of *P. falciparum* in human volunteer induced blood stage malaria studies.
- To investigate the use of  $^{18}\text{F}$  FDG-PET/MRI to estimate the biomass of *P. falciparum*.

Secondary:

- To describe the relative burden of organ-specific tissue sequestration in *P. falciparum*.
- To describe the impact of early malaria infection on glucose metabolism.
- To describe the MRI brain findings of early malaria infection in a prospective participant cohort.

### i. Research Question

The present EXPLORATORY STUDY has been designed to establish the role of  $^{18}\text{F}$  FDG-PET/MRI in studying the pathophysiology of subpatent malaria following low dose *Plasmodium falciparum* exposure in healthy adults.

### ii. Study Outcome Measures

Primary

The primary objective of the study is to assess the application of whole body  $^{18}\text{F}$  FDG-PET/MRI in describing the parasite biodistribution and biomass in subpatent malaria. This is a hypothesis generating pilot investigation expected to have predominately descriptive outcomes.

The primary outcome measures will be the quantified and semi-quantified  $^{18}\text{F}$  FDG uptake values from specific regions of interest. Regions of interest for quantification of uptake will be spleen, bone marrow (lumbar spine and/or pelvis), muscle bulk (quadriceps) and brain. Post inoculation measurements will be compared to baseline pre inoculation uptake values. Biochemical markers of parasitaemia and total biomass from MAIN study data will be compared to  $^{18}\text{F}$  FDG uptake values.

Any other regions of interest (as deemed by the investigators) identified after imaging will have semi-quantified  $^{18}\text{F}$  FDG uptake values calculated for further comparison.

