## **3. STUDY DESIGN**

This is an EXPLORATORY STUDY comprising a population recruited from a single-center, IBSM model MAIN study. This EXPLORATORY STUDY is a pilot investigation to establish the role of  $^{18}\text{F}$  FDG-PET/MRI in studying the pathophysiology of subpatent malaria. The population will consist of two healthy adults inoculated with *P. falciparum* from existing MAIN study population.

MAIN study refers to the parallel IBSM MAIN study QP15C20 SJ733

Participants will receive **two** whole body PET/MRI scans: the first within one week prior to MAIN study inoculation and the second one to two days prior to confinement with peak parasitaemia post BSP inoculation (estimated MAIN study InD 6 to 7). Blood samples will be collected at MAIN study timepoints.

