### **Preparation:**

At screening, participants will be consented for EXPLORATORY STUDY inclusion. At the time of consent the participant and study doctor will complete the MRI checklist (see Appendix B) and education regarding pre-imaging preparation. In the 24 hours prior to image collection, a low carbohydrate diet is to be followed, and strenuous exercise is to be avoided. These activities are to be recorded on the provided diet and activity sheet (see Appendix C).

On the day of imaging, participants are advised to wear warm clothing and arrive fasted for 6 hours prior (water is permitted, and good hydration encouraged). Participants will arrive to HIRF where the MRI checklist and diet and activity checklist will be reviewed. A peripheral intravenous cannula will be inserted for radiotracer administration. A bedside blood glucose measurement will be measured if there is

clinical suspicion of a blood glucose abnormality.

Whole body imaging will be performed on the Biograph mMR PET/MRI system after the intravenous infusion of the radiotracer  $^{18}\text{F}$  FDG. Dynamic tracer uptake will be recorded over a 45-60 minute period from the abdomen for quantitative measurement of FDG uptake in the spleen. Participants will be offered a short break, followed by collection of static images of the whole body and brain, over an estimated 30 minute period.

Dedicated brain imaging will take place using the MAGNETOM Prisma 3T MRI system. This includes MP2RAGE, T2FLAIR and diffusion weighted MRI sequences of the brain for assessment of the effects of very subtle oedema and inflammatory responses. The estimated time of image acquisition is 45 minutes per patient. Depending on initial results, there may be some changes to MRI sequences to improve data collection. Participant activities or exposures will not be affected by any technical imaging sequence change.

Following image acquisition participants will be allowed food and drink and encouraged to drink water. Each HIRF visit is approximately 4 hours in total duration.

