#### **Image Interpretation:**

Collected images will be reviewed and reported by specialist radiologists at HIRF/RBWH. Imaging metrics (FDG uptake and kinetic parameters) will be compared between baseline and follow up scans. Quantitative  $^{18}\text{F}$  FDG uptake will be calculated using Patlak model analysis from dynamic uptake imaging, yielding a Ki value ( $^{18}\text{F}$  FDG influx constant.) A nominated region of interest will have quantitative  $^{18}\text{F}$  FDG uptake calculated for each scan. Semi-quantitative  $^{18}\text{F}$  FDG uptake will be calculated using SUVs measured during static uptake imaging. All regions of interest will have SUVs calculated.

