#### **Evaluation of data:**

All data will be presented descriptively. Pre and post inoculation quantitative imaging metrics will be compared with paired T-tests or Mann-Whitney U tests. Groups will be compared with unpaired T-tests with consideration of T-value adjustment for population size and Mann-Whitney U tests. Any groups identified based on imaging results will be described with respect to demographic, clinical and biochemical data collected as part of the MAIN study.

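### The two-participant protocol gives no reference for scan-to-scan variation against which an individual's pre/post change in FDG uptake can be read, and its planned tests cannot supply one with two people.

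*Supplement*

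**What the plan says.** All references are to the two-participant *P. falciparum* protocol. The eight-participant protocol is separately registered and does not replace it.

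- **Design (section 3).** "The population will consist of two healthy adults inoculated with" the parasite. Each has two scans: "the first within one week prior to MAIN study inoculation and the second one to two days prior to confinement". Neither scan is repeated.
- **Primary outcome (section 2.2 ii).** "Regions of interest for quantification of uptake will be spleen, bone marrow (lumbar spine and/or pelvis), muscle bulk (quadriceps) and brain". The comparison is: "Post inoculation measurements will be compared to baseline pre inoculation uptake values". Uptake is also compared with markers of parasitaemia and biomass, and further regions may be added after the images are seen.
- **Metrics (section 3).** For SUV, "All regions of interest will have SUVs calculated". The dynamic acquisition is "for quantitative measurement of FDG uptake in the spleen", giving a Patlak Ki there. The synopsis puts the analysis at the level of the individual: "uptake measurements will be established for intra-individual scans using Patlak model analysis", together with SUV referred to an FDG external control.
- **Evaluation (sections 3 and 10.2).** "All data will be presented descriptively". Pre and post values are also tested by paired t-test or Mann-Whitney U test, with significance at p < 0.05 in section 10.2.
- **Attribution (section 2.2 ii, Secondary).** The effect of early infection on glucose metabolism is to be evaluated from these same outcomes.
- **Control of variation.** There are fasting, diet and exercise rules (sections 3 and 5.1), a record of non-compliance and movement (section 5.3), and a statement that data quality will be described (section 9). Scan-day glucose is measured only on clinical concern.

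**The concern.** The informative result of this protocol is the change between two scans, region by region, in two people. One pair of scans says nothing about how far two scans of the same uninfected person would differ, and two pairs say almost nothing. The preparation rules should reduce that variation, but they do not say how much remains. An external control speaks to scanner calibration, not to day-to-day biological variation, and no tolerance is attached to it.

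The reader of the report will see that uptake in some region rose by some percentage and will have no planned means of judging whether that is more than repeat-scan noise. A chance rise could then point the next study at the wrong organ. A real rise could not be defended as real. Section 10.1 says the data may feed later power calculations, so the point matters even for a pilot.

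**Working it through.** The protocol has no power calculation or repeatability figure, so there is no stated number to reproduce.

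**Inputs from the protocol.** Two participants, with one baseline and one post-inoculation scan each. Five metrics per person are named in advance: SUV in four regions, plus Ki in the spleen. That makes 2 x 5 = 10 individual changes. The significance level is 0.05, taken as two-sided because sidedness is not stated.

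**Assumed, not in the documents.** Within-person CV of 5%, 10% or 15%, the same for every metric. Normal errors. No true effect of infection. An illustrative cut-off of 20% for calling a change notable. Correlation between metrics within a person of 0 or 0.8.

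**Step 1. Can the section 10.2 tests act as the yardstick?**
- Paired t-test, n = 2: 1 degree of freedom, critical |t| = 12.7. Power is about 18% for a mean change of 2 SDs of the change, and 42% for 5 SDs.
- Mann-Whitney, 2 v 2: smallest two-sided p = 2/C(4,2) = 2/6 = 0.33, so it can never reach 0.05.
- Chance of at least one false p < 0.05 over five t-tests: 1 - 0.95^5 = 23% if independent, about 20% at correlation 0.8.

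**Step 2. Size of noise in one pre/post change.** SD of the percentage change = sqrt(2) x CV. The 95% repeatability limit = 1.96 x sqrt(2) x CV. P(one change exceeds 20%) = 2 x [1 - Phi(20/SD)]. P(at least one of ten) = 1 - (1 - p)^10 if independent; the values at correlation 0.8 are simulated.

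| Assumed CV | SD of change | 95% limit | p, one change over 20% | Any of 10, independent | Any of 10, correlation 0.8 |
|---|---|---|---|---|---|
| 5% | 7.1% | 13.9% | 0.005 | 5% | 3% |
| 10% | 14.1% | 27.7% | 0.157 | 82% | 57% |
| 15% | 21.2% | 41.6% | 0.346 | 99% | 88% |

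**Step 3. A check that needs no CV.** With no effect, each change is as likely up as down, so both people rise in a given metric with probability 0.25. The chance that both rise in at least one of five metrics is 1 - 0.75^5 = 76% if independent, and 46% at correlation 0.8.

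**Step 4. What a limit alone achieves.** With a 95% limit per metric, the expected number of null changes outside it is 10 x 0.05 = 0.5. The chance of at least one is 1 - 0.95^10 = 40% if independent and 24% at correlation 0.8. So a limit needs a companion rule.

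**Step 5. Adding agreement between participants.** Both outside the limit in the same direction in one metric: 2 x 0.025^2 = 0.00125. In at least one of five metrics: 1 - (1 - 0.00125)^5 = 0.6% if independent, about 0.5% at correlation 0.8.

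**The case against.** The protocol calls itself a hypothesis-generating pilot with mainly descriptive outcomes, and no treatment or go/no-go decision hangs on any region's change. It standardises preparation, records non-compliance, refers SUV to an external control and promises to describe data quality. Uptake is also set against parasitaemia and biomass, so the reading does not rest only on which regions rose. All of this stands and limits the consequence. None of it gives a size for scan-to-scan variation.

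Three stronger readings are tempting, and the documents do not support them.

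- **That a false signal is likely.** This depends on the CV and the cut-off, neither of which is in the documents. At a CV of 5% the chance is only 3-5%. With independent metrics it passes one half only above a CV of about 7.7%. By the p < 0.05 criterion alone it is about one in five.
- **That the regions reported as changed will mostly be noise.** Every figure above assumes no effect of infection. No effect size is given, so the share of observed changes due to noise cannot be known.
- **That the plan treats any difference as a change.** It does not say so. It describes, and it names a test with a threshold. The difficulty is that the test tells the reader next to nothing at n = 2.

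**Conclusion.** The point holds as a gap in how individual changes will be interpreted. Changes are to be described and related to infection without any reference for repeat-scan variation, and the significance tests cannot stand in for one in two people. That part rests on the documents and on exact arithmetic.

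Its practical size is uncertain: from negligible (3-5%) to near-certain (88-99%) over assumed CVs of 5% to 15%, with a 20% cut-off chosen for illustration and one CV applied to all metrics. That this range cannot be narrowed from the protocol is itself the reason to look the figure up. The change is worth making because it is cheap. It is not a fault that invalidates the pilot.

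**What to change.** Add to section 3 (Evaluation of data) and section 10.2:

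- Before any post-inoculation scan is analysed, fix a 95% repeatability limit, 1.96 x sqrt(2) x within-person CV, for spleen Ki and for SUV in each named region. Take it from site or published test-retest data, and state the source and the range.
- Show each participant's percentage change against its limit. Report a change inside it as not distinguishable from repeat-scan variation.
- State that about 0.5 of ten null changes would fall outside the limits by chance, with a 24-40% chance of at least one. Describe a change as a possible infection signal only if both participants exceed the limit in the same direction.
- Label regions chosen after imaging as post hoc.
- Where no suitable test-retest data exist for a metric, say so and do not attribute its change to infection.

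The cost is a search for test-retest data and one paragraph of text, with no added scans, radiation or participants. There are two downsides. Limits borrowed from another scanner are approximate, and suitable data may not exist for every metric. The two-participant rule also costs sensitivity: if the true change equals the limit, each person exceeds it about half the time, so both do so about 0.5 x 0.5 = 25% of the time. Single excursions should therefore still be shown, without attribution.

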### Secondary

The relative burden of organ specific sequestration will be determined by comparing  $^{18}\text{F}$  FDG uptake values for each region of interest.

The impact of early malaria infection on glucose metabolism will be evaluated in assessing each of the above outcomes.

The MRI findings of early malaria will be presented in a descriptive manner, outlining any interval changes in high-resolution brain MRI for this prospective cohort.

## **iii. Study Rationale**

This EXPLORATORY STUDY has been designed to establish the role of  $^{18}\text{F}$  FDG-PET/MRI in studying the pathophysiology of subpatent malaria. The selection of this radiotracer and imaging modality offers a well-validated model for exploring nuclear medicine functional imaging of malaria infection in a healthy human volunteer population.

### **Hypotheses**

- Whole body  $^{18}\text{F}$  FDG-PET/MRI is a technically feasible imaging modality for the study of subpatent malaria infection.
- Quantitative and semi-quantitative uptake of  $^{18}\text{F}$  FDG is proportional to estimated parasite biomass and parasitaemia.
- Subtle changes in the vasculature of the brain are present and identifiable on MRI imaging in subpatent malaria infection.

## **iv. Potential Risks and Benefits**

### Potential Risks

There is a small risk associated with radiation exposure from the radiotracer  $^{18}\text{F}$  FDG. This falls into the low risk category of the ARPANSA guidelines. This is outlined in the radiation assessment report (Appendix A). There is a small risk of perturbation in blood glucose levels following  $^{18}\text{F}$  FDG administration. To minimize

this risk all participants will undergo blood glucose testing at screening and further testing prior to any administration if there are clinical concerns to ensure they are suitable to receive the radiotracer. There is a very small risk of a reaction to the infusion of the radiotracer  $^{18}\text{F}$  FDG. This is outlined in section 8.4. A product information sheet for  $^{18}\text{F}$  FDG will be provided to each participant (Appendix G.)

There is the risk of incidental abnormalities being identified on whole body PET/MRI imaging. These will be managed on an individual basis in consultation between the reporting radiologist, study doctor, principal investigator and participant.

Other risks, including those associated with IBSM inoculation and blood collection are as described in the MAIN study. EXPLORATORY STUDY involvement is not expected to alter these pre-existing risks.

